# The effect of patient-led goal setting approach combined with pain neuroscience education or manual therapy in patients with chronic low back pain: protocol for a parallel-group randomized controlled trial

**DOI:** 10.1186/s13063-023-07617-1

**Published:** 2023-09-08

**Keywords:** Patient-led goal setting, Pain neuroscience education, Chronic low back pain, Manual therapy

## Abstract

**Background:**

Low back pain (LBP) is a multifactorial disorder associated with a high range of physical and psychological burden on the society. Patient-led goal-setting approach has shown potential effects for improving chronic LBP. However, there are few studies investigating its benefits when combined with a supplementary intervention. This paper, therefore, presents a protocol for a randomized control trial (RCT) to study the effect of a patient-led goal-setting approach combined with pain neuroscience education (PNE) or manual therapy (MT) among patients with chronic LBP.

**Methods:**

A total of 105 patients suffering from chronic LBP will be recruited via flyers displayed in hospitals and universities, and those meeting the study’s criteria will randomly be allocated into a patient-led goal-setting approach with the PNE group, and/or with the MT program group, and/or a control group. The primary outcomes will be the pain intensity and disability. Secondary outcomes include quality of life, depression, anxiety and stress, fear avoidance beliefs, kinesophobia, pain self-efficacy, catastrophic pain, neurophysiology of pain, and central sensitivity. All the outcomes will be recorded at 2 months after receiving the treatment as post-test sessions and after 4 and 12 months as follow-up sessions. The Ethics Committee in Research at Sport Sciences Research Institute of Iran approved the protocol of this trial (IR.SSRC.REC.1400.084). Written, informed consent to participate will be obtained from all participants. All methods will be conducted in accordance with the ethical standards of the Declaration of Helsinki and in accordance with relevant guidelines and regulations. We will disseminate the findings through peer-reviewed publications and conference presentations and send them to the participants.

**Discussion:**

This trial will demonstrate which supplementary intervention can better improve the impact of a patient-led goal-setting approach to treat LBP. If successful, the results will potentially have implications for athletic trainers, physiotherapists, and health care practitioners.

**Trial registration:**

IRCT Iranian Registry of Clinical Trials IRCT20210927052616N1. Registered on November 03, 2021.

**Supplementary Information:**

The online version contains supplementary material available at 10.1186/s13063-023-07617-1.

## Strengths and limitations of this study

This is the first study to investigate primarily the effect of the patient-led goal-setting approach and PNE compared with the patient-led goal-setting approach and MT on pain intensity, disability, and quality of life in patients with chronic LBP.The secondary aim of this study is to investigate the effect of patient-led goal-setting approach and PNE compared with the patient-led goal-setting approach and MT on psychological and psychological factors in patients with chronic LBP.This trial will demonstrate which supplementary intervention can better improve the impact of a patient-led goal-setting approach to treat LBP.If successful, the results will potentially have implications for athletic trainers, physiotherapists, and health care practitioners

## Introduction

Low back pain (LBP) is one of the most common causes of disability across the world [1]. More than 85% of patients with LBP receiving primary care have experienced pain chronification [2]. Chronic LBP contributes to a highly significant burden on society and individuals, e.g., health-related costs, individual quality of life, and disability across the world [3]. Due to physiological and psychological factors behind the chronic type of LBP, it is associated with limitations in daily routines, kinesiophobia, and disability.

Some of the most widely used therapies in chronic LBP include pharmacotherapy, invasive therapies, biophysical and electrotherapy, exercise therapy, and/or manual therapy [2]. Nowadays, the lack of treatment interventions covering different and complex factors of LBP is obviously observed. Therefore, getting better results of exercise therapy, factors like knowledge of pain neuroscience and pain education and the role of psychosocial/cognitive and behavioral characteristics in pain are essential.

Meanwhile, self-management program as an effective intervention includes a goal-setting approach motivating the individuals to change their behavior in order to achieve a better result [4]. In self-management programs, there are two important factors needed to be considered. Self-determination and self-efficacy using a self-management approach can be achieved and can help patients identify problem areas of personal relevance associated with their condition, establish achieving goals, and applicable strategies [4]. In a self-management approach, the patient is encouraged to independently take the steps towards goal achievement and increase their sense of confidence and ownership in the goal setting skills [4, 5]. However, as a multifactorial type of chronic LBP, previously, it has been widely shown that better results can be obtained when a specific intervention is combined with a supplementary one [3].

Pain neuroscience education (PNE) is a psychological-based supplementary intervention aiming to change patients’ understanding about their pain and unhelpful beliefs. In PNE, the patient is taught about the physiology of pain, nociceptive pain, displaying different parts of the body in the brain, pain-related changes in body perception, and the psychological dimensions of pain [6].

Furthermore, manual therapy (MT) is also one of the most cost-effective and low-risk treatments for chronic LBP [7]. MT can be defined as mobilization and manipulation techniques for relieving pain and musculoskeletal dysfunction. MT is also associated with neurophysiological effects such as changes in the activity of alpha motor neurons and autoimmune response systems and an increase in blood levels of endorphin and serotonin, which have been shown to occur throughout the nervous system through peripheral, spinal, and supra-spinal mechanisms [7, 8].

In the previous studies [9–11], most therapeutic approaches to the treatment of chronic LBP were consistent with biomedical models. In these models, the focus is on structural and biomechanical disorders. Recent studies have shown that pain has sensory, behavioral, and psychological components, and the association of chronic LBP with psychological, behavioral, and social factors has been established. As a result, new biopsychosocial models for the treatment of chronic pain have been introduced, but the implementation of these approaches is not yet common, and a very limited number of studies have examined the multidimensional treatment of chronic LBP. Therefore, because of the lack of evidence supporting the benefits of a combined cognitive-based intervention’s effect, this randomized control trial (RCT) will investigate the effects of a patient-led goal-setting approach combined with PNE or manual therapy in patients with chronic LBP. It is hypothesized that intervention combined with PNE can show a better result especially on psychological outcomes.

## Aims

Primary aim: Investigating the effect of a patient-led goal-setting approach and PNE compared with a patient-led goal-setting approach and MT on pain intensity, disability, and quality of life in patients with chronic LBP.

Secondary aim: Investigating the effect of a patient-led goal-setting approach and PNE compared with a patient-led goal-setting approach and MT on psychological factors in patients with chronic LBP.

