### Statistical analysis

The data will be summarized with descriptive statistics (mean, median, standard deviation, percentiles for numerical variables, frequencies and percentages for categorical variables). The SPSS software version 26 will be used to analyze the data. The Shapiro–Wilk test will be used to examine the normal distribution of data. If the normal distribution is approved, the mix model ANOVA will be used to compare the differences in scores related to each variable in the pre-test and post-test in each group (with-in group effects) and to examine the differences between groups in each time point (between group effects), and Bonferroni post hoc test will be used to find significant differences and compare the groups. This model allows for possible missed data. We will assume data missing at random. Study group and time of assessment will be used as fixed factors and patients will be used as random factors. Otherwise, the Mann–Whitney *U* test will be used to compare two independent groups in case the normal distribution was not approved. Finally, after post hoc tests, the Cohen test (*d*) will be used in order to calculate the effect size [24]. *P*-value < 0.05 will be considered significant. The main conclusion will be drawn from the unadjusted analysis without performing any subgroup analysis of primary and secondary outcomes.

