## Discussion

The aim of this study will be to compare the effect of patient-led goal-setting approach combined with PNE or MT in patients with chronic LBP. The main question of this study is whether the patient-led goal-setting approach combined with PNE is more effective than MT in reducing pain intensity related with chronic LBP. Further objectives will be also to assess the effect of these two interventions on disability, quality of life, and psychosocial factors in chronic LBP compared to a control group. A total of 105 patients will participate in this study and the athletic trainer who performs the pre-test and post-test as well as follow-up evaluations will be blinded to the participants’ group code. It is expected that this RCT will provide novel data on the effectiveness of the patient-led goal-setting approach combined with PNE or MT in patients with chronic LBP compared to a control group.

In the current study, we will evaluate the effects of combined interventions on psychological outcomes as well as central sensitivity. It is expected that this prospective trial may contribute towards refining guidelines for good clinical practice and may be used as a basis for health authorities’ recommendations. If successful, the findings and information provided by this study will potentially have implications for physiotherapists, athletic trainers, and health care practitioners.

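### The protocol gives three different primary outcome sets and no primary visit, and its analysis section does not single out the contrast that the aims name as primary

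*Protocol article*

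**What the plan says.** **Primary outcomes.** Three versions stand in the protocol article.

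- *Aims*, repeated in *Strengths and limitations of this study*: the primary aim sets goal setting plus PNE "compared with a patient-led goal-setting approach and MT on pain intensity, disability, and quality of life in patients with chronic LBP". That is three outcomes.
- *Abstract, Methods*: "The primary outcomes will be the pain intensity and disability. Secondary outcomes include quality of life". The *Primary outcomes* and *Secondary outcomes* headings in the body make the same split. That is two outcomes, with quality of life secondary.
- *Discussion*: "The main question of this study is whether the patient-led goal-setting approach combined with PNE is more effective than MT in reducing pain intensity". Disability and quality of life come afterwards: "Further objectives will be also to assess the effect of these two interventions on disability, quality of life, and psychosocial factors", there in comparison with control. *Sample size estimation* also rests on pain.

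**Contrast.** Aims, Strengths and limitations, and Discussion all name goal setting plus PNE versus goal setting plus MT.

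**Visits.** Outcomes are measured at baseline and at 2, 4 and 12 months. The 2-month visit is called the post-test and the later two follow-up. None is called primary.

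**Analysis.** *Statistical analysis* uses a mixed-model ANOVA "to examine the differences between groups in each time point (between group effects), and Bonferroni post hoc test will be used". The threshold is a P-"value < 0.05 will be considered significant". The post hoc step serves to compare the groups. The section does not pick out PNE versus MT and states no adjustment over outcomes or visits.

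**The concern.** Quality of life is both primary and secondary, and disability is both primary and a further objective. An analysis plan written under this protocol would have to inherit one of the versions, and nothing in the text says which.

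The consequence is practical. Suppose the arms differ on quality of life at 12 months but not on pain at 2 months: the report could cite the Aims and call the trial positive. Given the reverse result, it could cite the Discussion. The outcome and visit that decide the trial can then be chosen after the data are seen, and the 5% level describes a single test rather than the trial's conclusion.

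**Working it through.** **Inputs from the protocol article.** Three arms, so three group pairs; three post-baseline visits; significance level 0.05; Bonferroni for the group comparisons; 1, 2 or 3 primary outcomes depending on the section; 105 patients in total.

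**Assumptions not in the document.** Equal allocation (105/3 = 35 per arm); two-sided tests; Bonferroni divisor 3; quality of life as a single score; correlations between visits and between outcomes from 0 to 0.7; a significant result at any visit counts; post hoc tests are not conditional on a group-by-time test.

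**Step 1: the plan's own figures.** The document states no familywise error rate, only 0.05. For one outcome at one visit, with three pairs at 0.05/3 = 0.0167, simulation gives 4.4%. The Bonferroni step therefore does its job within one outcome and one visit.

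The stated 15 per group can also be reproduced, as a group-by-time interaction with 0.25 read as Cohen's *f* (not *d*), four measurements, and an assumed correlation of 0.5:

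- λ = f² × N × m / (1 − ρ) = 0.0625 × 45 × 4 / 0.5 = 22.5
- degrees of freedom (3−1)(4−1) = 6 and (45−3)(4−1) = 126
- power 0.955 at N = 45

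This describes a repeated-measures test, not a pairwise test at one visit.

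**Step 2: bounds under independence.** With k outcomes × 3 visits:

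- Named contrast only, at 0.05/3: 1 − (1 − 0.05/3)^(3k) = 4.9%, 9.6% and 14.0% for k = 1, 2, 3.
- Any pair, each outcome-by-visit family held at 0.05: 1 − 0.95^(3k) = 14.3%, 26.5% and 37.0%.

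**Step 3: simulation under no effect.** 100,000 trials per setting, 35 per arm, pooled-variance t tests at 0.05/3, any of three visits counting. The correlation shown applies both between visits and between outcomes.

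| Primary outcomes | What counts | Corr. 0 | Corr. 0.5 | Corr. 0.7 |
|---|---|---|---|---|
| Pain | PNE vs MT | 4.9% | 4.5% | 3.9% |
| Pain, disability | PNE vs MT | 9.7% | 8.3% | 6.7% |
| Pain, disability, quality of life | PNE vs MT | 14.0% | 11.6% | 9.1% |
| Pain | any pair | 12.6% | 11.2% | 9.8% |
| Pain, disability | any pair | 23.6% | 20.0% | 16.3% |
| Pain, disability, quality of life | any pair | 33.0% | 27.2% | 21.4% |

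**Step 4: effect of a gate.** Requiring a significant overall F at each visit changes little: 19.3% instead of 20.0% for two outcomes, any pair, correlation 0.5 (20,000 trials). If post hoc tests ran only after one significant group-by-time test per outcome, the rate under no effect would be at most 1 − 0.95² = 9.8% for two outcomes and 1 − 0.95³ = 14.3% for three. The Statistical analysis section does not say whether such a gate applies.

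**The case against.** **The contrast is named.** A reader might infer from the all-groups analysis that the trial has no primary contrast. The document does not support that. Three sections give PNE versus MT, and comparisons with control appear in the Discussion only among further objectives. What stands is narrower: the analysis section does not carry the named contrast through.

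**A headline error rate of 20–25% is not a property of the plan.** It needs pairs involving control to count as primary, two or three primary outcomes, any visit to count, and particular correlations. For the named contrast with the stated Bonferroni step the rate is lower, and for pain alone it stays under 5%. Testing PNE versus MT at an unadjusted 0.05 would give higher figures (22% for two outcomes at correlation 0.5), but that drops a correction which the plan states.

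**Part of this is silence rather than contradiction.** A journal article may leave multiplicity over outcomes and visits to an analysis plan, and calling 2 months the post-test does set that visit apart. That is fair for the adjustment method. It does not cover the outcome set, where sections of the same article disagree, and the post-test label is not a designation as primary.

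**Conclusion.** The point holds as a contradiction over the primary outcomes, with no primary visit and with a named contrast that the analysis section leaves untied.

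The inflation is conditional. For PNE versus MT at 0.05/3 it is about 4–5% (pain), 7–10% (two outcomes) and 9–14% (three). If any of the three pairs may count, it is about 10–13%, 16–24% and 21–33%. These ranges rest on the assumptions listed above, chiefly correlations of 0 to 0.7 that the document does not give; a group-by-time gate would lower the all-pairs figures.

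Only the reading with pain alone, the named contrast and the Bonferroni divisor of 3 keeps 5% across the three visits, and the protocol does not commit to it. The contradiction needs to be resolved whatever the exact rate, because it decides what the trial can conclude.

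**What to change.** Before unblinding:

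1. State one primary hypothesis that follows the protocol's own main question: pain on the NRS, goal setting plus PNE versus goal setting plus MT, at one prespecified visit, two-sided 5%. The 2-month post-test is one option; the sponsor may choose another single visit.
2. Tie the Statistical analysis section to that test.
3. If disability is to stay primary, test it in fixed sequence after pain, or use a Holm adjustment over the two.
4. Label quality of life, comparisons with control and the other visits as secondary.
5. Align the Abstract, Strengths and limitations, Aims, Primary and Secondary outcomes, Statistical analysis and Discussion sections, and update the registry, as the Protocol amendments section already provides.

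**Cost.** Mostly wording. Quality of life, the other visits and, unless step 3 is used, disability lose primary standing. The sample-size statement must also be redone. It shares only the outcome, pain, with this hypothesis, since it describes a repeated-measures analysis. If its 0.25 is taken as labelled, as Cohen's *d*, a pairwise test at one visit with 35 per arm has about 18% power, so the effect that the primary test is meant to detect has to be stated and justified.

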## Methods

### Study design and setting

This study is a three-arm single-blind RCT approved by the Ethics Committee in Research at Sport Sciences Research Institute of Iran (IR.SSRC.REC.1400.084) with the IRCT registration number IRCT20210927052616N1 and will be carried out in the Sport Medicine Laboratory of Kharazmi University of Iran. The CONSORT diagram for this study is provided in Fig. 1.

**Fig. 1 Fig1:**
[figure not shown]
CONSORT diagram

### Recruitment

We will recruit patients through practitioners via flyers distributed at Kharazmi University, hospitals, and physical therapy clinics. We will further use advertising posters in each center and online advertisements in the media. Then, participants will be in charge of screening for inclusion and exclusion criteria, and a final decision will be taken regarding the eligibility of the patients.

### Informed consent

Prior to the enrollment, all the participants will be fully informed about the objectives of the study and will provide written informed consent. Research assistants will obtain informed consent. The chief investigator retains overall responsibility for the informed consent of participants and will ensure that all those with delegated responsibility are authorized, trained, and competent to participate according to the protocol, principles of Good Clinical Practice (GCP), and Declaration of Helsinki.

### Eligibility criteria

The patients who participated in this study will be 105, both men and women aged between 18 and 65 years with chronic or recurrent LBP for > 3 months, pain intensity of 4 out of 11 Numerical Rating Scale (NRS), and at least 20 scores reported on the Quebec Back Pain Disability Scale (QBPDS) [5]. Those patients with a history of specific causes of LBP (e.g., systemic, rheumatic, neuromuscular diseases), central or peripheral neurological signs, psychological impairment, spinal surgery, or physical therapy treatments in the last 6 months prior to the baseline assessment will be excluded from the study. Criteria assessment will be performed by an experienced physical therapist.

### Allocation

Block randomization will be used in this study. A person not involved in the execution of the trial generates the randomization list using block randomization via computer-generated random numbers. The same person prepares sealed envelopes containing the treatment allocation information. The block size is not revealed to the study group before analyses. The envelopes are stored in a secure place at the study center. After receiving the informed consent, a researcher who did not apply the intervention (treatment approaches) or evaluate the outcomes gives a sealed envelope to the patient containing the treatment allocation information, and the treatment is arranged accordingly.

### Blinding

The blind researcher will be blinded from the treatment allocation when collecting the outcome measurements. The patient will be wearing long-covered clothes during the follow-up visits and asked not to reveal the given treatment. The blinding of the treatment approach is not possible for the personnel executing the treatment approach nor the patients. This study will be conducted as a pre-test/post-test design with a control group and blinded assessor and data analyst.

### Description of the interventions

#### Patient-led goal-setting approach

The intervention will be carried out for 8 weeks including 5 face-to-face sessions. The first session takes about 1 h, and the other sessions are held for 15 to 30 min with 2-week intervals. Then, two follow-up sessions (lasting 30 min each) will be developed with a 1-month interval; furthermore, one session will be organized 12 months after the first session, and finally, the results will be collected. The SMART model will be used for applying this intervention. This model includes a special process for goal setting that is measurable, achievable, and associated to a specific time return. In this model, the researcher is trained in setting goals by the patient, considers the patient’s history of LBP, and discusses about the issue that led to the occurrence of LBP [4]. Patients are asked to prioritize these problems based on what they want to focus on. Then, the strategies are discussed based on evidence-based guidelines, and the patient sets specific goals and strategies to work independently between sessions. Patients record their set goals, progress towards these goals, and agree on strategies for achieving the goal in their workbooks. If the goal strategies include consultation with a health care professional, the patient is encouraged to pursue this independently (Table 1) [3–5].

**Table 1 Tab1:** Components of the interventions

Patient-led goal-setting intervention
Session 1: week 1
► Orientation of patient
► SMART approach explained
► Goals and strategies developed
Homework task: review educational material
Session 2: week 3
► Education and discussion
► Review of goals, progress towards, and barriers to achieving goals
► Strategies developed
Sessions 3 and 4: weeks 5 and 7
► Review of goals, progress towards, and barriers to achieving goals
► Strategies developed
Session 5 (completion of the intervention): 2 months
► Review of goals, progress towards, and barriers to achieving goals
► Strategies developed
► Outcomes measured
Post-intervention follow-up (3 months)
► Review of goals, progress towards, and barriers to achieving goals
Post-intervention follow-up (4 months)
► Review of goals, progress towards, and barriers to achieving goals
► Outcomes measured
Post-intervention follow-up (12 months)
► Outcomes measured

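### At 2 and 4 months the outcomes are listed inside the goal-setting visits, after the goal review, and time zero is worded inconsistently with no anchor that exists for controls

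*Protocol article*

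**What the plan says.** **Place of measurement.** In the section on the patient-led goal-setting approach, Table 1 sets out the content of each goal-setting visit. The post-test entry is "Session 5 (completion of the intervention): 2 months". Its items are a review of goals, progress and barriers, then strategy development, then outcome measurement. The entry "Post-intervention follow-up (4 months" lists the goal review and then outcome measurement. The 12-month entry contains outcome measurement only. Under Description of the control, controls receive a pamphlet and no sessions.

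**Who measures.** Under Blinding: "The blind researcher will be blinded from the treatment allocation when collecting the outcome measurements". The same section says that neither patients nor treating personnel can be blinded. The Implementation section has a blinded assessor at baseline, and the Discussion has a blinded trainer for all evaluations.

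**Time zero.**
- Abstract, Methods: "All the outcomes will be recorded at 2 months after receiving the treatment as post-test sessions".
- Goal-setting text: "The intervention will be carried out for 8 weeks including 5 face-to-face sessions", and for the last visit "one session will be organized 12 months after the first session".
- Table 1, for that same last visit: "Post-intervention follow-up (12 months", with the months in brackets.
- Outcome measures and Table 3: baseline or start, then 2, 4 and 12 months in all three arms, with no event named from which the months are counted.

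**The concern.** There are two separate weaknesses.

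First, pain, disability and the secondary outcomes are all patient-reported, and the patients know their treatment. A review of goals, progress and barriers just before the questionnaires may colour the answers. A blinded assessor does not remove that, because the influence acts on the patient. Only the active arms have such a review. The Discussion states comparison with the control group as an objective, so part of an active-versus-control difference at 2 or 4 months could reflect the circumstances of measurement.

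Second, a post-test at the end of treatment and a post-test 2 months after it answer different questions: immediate effect or short-term persistence. Controls have neither a first session nor an end of treatment, so neither anchor can be applied to them as worded.

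**Working it through.** **Inputs.** Goal setting has 5 sessions over 8 weeks, with spacing "the other sessions are held for 15 to 30 min with 2-week intervals". Two further sessions follow at a 1-month interval (Table 1: months 3 and 4). PNE has 4 weekly sessions. MT runs for 6 weeks. Conversion: 52.1775 / 12 = 4.348 weeks per month.

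**1. The plan's own 2 months.** Five sessions have 4 gaps of 2 weeks, so they fall in weeks 1, 3, 5, 7 and 9. Session 5 is 4 × 2 = 8 weeks after session 1, and 8 / 4.348 = 1.84 months. This agrees with the stated 2 months, and the sessions at months 3 and 4 then follow at 1-month steps. Table 1 is therefore internally consistent on a first-session clock, despite its post-intervention labels.

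**2. The same visit labels on two clocks.** If months are counted from the first session, time since the end of goal setting is label − 1.84. If they are counted from the end of goal setting, time since the first session is label + 1.84.

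| Visit label | Counted from first session: months after end of goal setting | Counted from end of goal setting: months from first session |
|---|---|---|
| 2 months | 0.16 | 3.84 |
| 4 months | 2.16 | 5.84 |
| 12 months | 10.16 | 13.84 |

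Each visit shifts by about 1.8 months. The abstract's post-test, read literally, lands almost on the other clock's 4-month visit.

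**3. If the abstract's treatment meant the add-on.** Assume that both add-ons start with the first session, which the article does not state. Two months are 2 × 4.348 = 8.7 weeks. The post-test then falls at week 4 + 8.7 = 12.7 for PNE and 6 + 8.7 = 14.7 for MT, against 8 + 8.7 = 16.7 if counted from the end of goal setting. The PNE and MT visits would be 2 weeks apart. Controls have no date to count from.

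**4. Where a goal review and outcome measurement share a visit.**

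| Visit | PNE arm | MT arm | Control |
|---|---|---|---|
| 2 months | review listed first | review listed first | no session |
| 4 months | review listed first | review listed first | no session |
| 12 months | no review | no review | no session |

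The two active columns are identical, so only active-versus-control comparisons at 2 and 4 months are exposed.

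**5. Can both fit in one session?** The item counts given under Outcome measures are 20 (QBPDS), 36 (SF-36), 21 (DASS), 10 (PSEQ), 16 (FABQ), 17 (TSK), 13 (PCS), 13 (RNPQ) and 25 (CSI). They sum to 171, or 172 with the NRS counted as one item. Session 5 lasts 15 to 30 minutes. Even if all 30 minutes went to questionnaires, that is 1,800 / 172 ≈ 10.5 seconds per item, with nothing left for the goal review. Measurement probably takes place outside the session proper, but the article does not say whether before or after it.

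**The case against.** The strongest reply is that the article already supports a sound reading. Table 3 gives every outcome the same start, 2-, 4- and 12-month columns in all three arms. The session dates fit a first-session clock, and the post-intervention label can be read as naming a phase. The longer clock then rests mainly on one phrase in the abstract. Blinding, Implementation and the Discussion all describe a separate blinded assessor, and the order of items in a table of components is not a procedure. Much of this stands, and it rules out several stronger readings that a reader might infer:

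- *The arms are measured at different times, or controls have no schedule.* Table 3 plans one schedule for all arms. Divergence is possible under loose wording but is not planned.
- *The treating researcher collects the outcomes.* Table 1 does not say who measures, and three sections say the assessor is blinded.
- *Active and control patients are assessed in different settings.* Nothing states where or how controls complete the questionnaires, so this is an inference.
- *The order favours the active arms.* The direction is not given. Reviewing barriers could also worsen ratings.
- *The primary comparison is compromised by priming.* Both active arms have the same goal-setting visits.
- *Unequal component lengths are a measurement fault.* The add-ons differ by 2 weeks between arms, but goal setting ends at session 5 in both. Differing length belongs to the treatments being compared.

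What the reply does not remove is that the abstract contradicts Table 1 on the post-test, that neither treatment-based anchor exists for controls, and that the only order shown puts the goal review before the self-reports. Detailed visit procedure may well be in the full protocol, but the order and the labels printed here still need correcting.

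**Conclusion.** The point holds in a limited form.

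*Measurement.* Active-versus-control comparisons at 2 and 4 months are open to bias if the listed order is followed in practice. Neither size nor direction can be derived from the document. By design the PNE-versus-MT contrast and the 12-month visit are not exposed to this.

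*Clock.* The statements of time zero conflict. The literal abstract reading differs from the first-session reading by about 1.8 months at each visit (about 3.8, 5.8 and 13.8 months instead of 2, 4 and 12). A common schedule from the start is the more likely intention. The 1.8 months rests on the stated 2-week spacing. The 2-week PNE-versus-MT gap in step 3 rests on an assumed common start and on reading treatment as the add-on, so it shows what the wording permits and not what is planned.

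This should be corrected: the change is small, and it settles both what the post-test measures and how controls are aligned with the active arms.

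**What to change.** 1. In the abstract, the goal-setting text with Table 1, and Outcome measures with Table 3, use one time zero that exists in all three arms (randomisation or baseline). Give the 2-, 4- and 12-month assessments one common window around it. Drop or reword the post-intervention labels so that they cannot be read as a second clock.
2. In Table 1, list outcome measurement ahead of the session content. State that the blinded assessor collects all questionnaires in the same way in every arm, before any goal-setting content that day.
3. Recruitment began in October 2021 (Trial status), so some visits may already have taken place. For these, report the actual assessment dates from the chosen time zero by arm, and whether the questionnaires came before or after the goal review.

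The cost is wording and the order of tasks within existing visits. No visit or staff is added and no treatment content changes. The downside is that completed visits cannot be altered, so some data may have been collected in the other order.
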